## The characteristics of central response of acupuncture for treating migraine

## The purpose of study

The purpose of this study is to compare the differences in brain activities evoked by active acupoints, inactive acupoints and acupoints on other meridians to investigate the possible correlation between clinical efficacy and brain responses.

## 2. Object of study

### 2.1 Recruitment

Subjects suffered migraine without aura will be recruited from the neurology department of the Teaching Hospital of Chengdu University of Traditional Chinese Medicine (TCM).

### 2.2 The choice of migraine patients

2.2.1 Diagnostic criteria

The diagnosis of migraine without aura is established according to the classification criteria of the International Headache Society (IHS) published in 2004.

2.2.2 Inclusion criteria

1. match the diagnosis of migraine patients without aura from the classification criteria of the International Headache Society (IHS) aforementioned;
2. all subjects are right-handed, and 2 to 8 migraine attacks per month during the last 3 months and during the baseline period (4 weeks before enrolment);
3. all subjects are 18 to 55 years of age; in addition, start of headache should be before the age of 50 years;
4. have received education for more than 6 years and have completed baseline headache diary;
5. have not taken any prophylactic headache medicine or any acupuncture treatment during the last 3 months;
6. no contraindications for exposure to a high magnetic field;
7. sign the written informed consent.

2.2.3 Exclusion criteria

1. existence of neurological diseases;
2. had hypertension, diabetes mellitus, hypercholesteremia, vascular/heart disease, and major systemic conditions;
3. pregnant or lactating women;
4. alcohol or drug abuse;
5. any neuroimaging research study participation during the last 6 months;
6. inability to understand the doctor’s instructions.

## 3. Method

### 3.1 Instrument and material

Instrument：3 Tesla Siemens MRI system (Allegra, Siemens Medical System, Erlangen, Germany)

Material：single use stainless steel filiform needles (Hwato Needles, Sino-foreign Joint Venture Suzhou Hua Tuo Medical Instruments Co., China); 25 mm-40 mm in length and 0.25 mm-0.30 mm in diameter

### 3.2 Sample size

20 subjects in each group

### 3.3 Study design

Randomization: using a computer-generated randomization sequence

Group assignment:

- Group A: acupuncture at active acupoints
- Group B: acupuncture at inactive acupoints
- Group C:acupuncture at acupoints on other meridians

Patients will be blinded to group assignment. Data management and analysis will be performed by researchers who are blinded to the acupuncture procedures.

Study schedule:

The total observation period within this study is 12 weeks for each patient. All patients will be asked to document their headache diaries, and the outcome measurement is completed both in the baseline and 4 and 8 weeks after randomization. Resting-state fMRI scans will be performed on each group before and after treatment to detect the local features of spontaneous brain activity.

### 3.4 Treatment schedule

3.4.1 Group assignment and acupoint selection

- Group A:SJ5 (Waiguan), GB20 (Fengchi), GB34 (Yanglingquan), GB40 (Qiuxu)
- Group B: SJ22 (Erheliao), PC7 (Daling), GB37 (Guangming), SP3 (Taibai)
- Group C: PC3 (Quze), PC6 (Neiguan), LR3 (Taichong), LR5 (Ligou)

3.4.2 SOP of manipulation

Traditional Chinese style acupuncture will be used and treatments are manipulated by specialized acupuncturists with at least five years’ training and three years’ experience.

The acupoints of all groups are asked to achieve *DeQi* sensation by lifting and thrusting combined with twirling and rotating the needles. All the groups are asked to retain the needles for 30 minutes, and close the acupoint holes with clean cotton balls to avoid bleeding when withdrawing the needle.

3.4.3 Treatment regimen

The total observation period within this study is 12 weeks for each patient. All patients should have recorded headache diaries for 4 weeks before randomization (baseline phase). After randomization the patients will receive 32 sessions of 30 minutes' duration over a period of 8 weeks (preferably 4 sessions in each week).

| -4 0 4（week） | | 8（week） |
| --- | --- | --- |
| baseline | treatment periods | |

### 3.5 fMRI scan

A standard eight-channel phase-array head coil is used, along with restraining foam pads to minimize head motion and to diminish scanner noise. Participants will be instructed to keep their eyes closed, relax, move as little as possible, and stay awake.

Scanning [parameters](app:ds:parameters): echo-planar imaging (EPI), TR=2000 ms, TE=30 ms, matrix=64×64, FOV=240 mm×240 mm, flip angle=90°, slice thickness=5 mm.

### 3.6 Outcome measurement

3.6.1 General information

gender, age, education level, vital signs, blood routine examination

These indicators will be filled and checked during the baseline.

3.6.2 Disease information

Patients met the inclusion criteria need to record the following information：

(1) disease history, family history, history of acupuncture treatment；

(2) headache diary：All patients fill in headache diaries during 4 weeks before randomization (baseline phase) and 4 and 8 weeks after randomization. The time of attack and stopping of headache, the intensity (VAS), the frequency, the location and the cause of headache, associated symptoms in each migraine attack. The patients document whether or not they take the medicine during treatment periods, and if patients take medicine they have to document the name, dosage of the medicine, the time of taking medicine, the time of relieving pain and the side effect of the medicine.

(3) others：the 6-item Headache Impact Test (HIT-6), the Zung Self-Rating Anxiety Scale (SAS), the Zung Self-Rating Depression Scale (SDS): document in the baseline and 4 and 8 weeks after randomization

(4) *Deqi* sensations: the feelings of *De-qi* will be collected after removing the needles during the 8^th^, 16^th^, 24^th^, and 32^nd^ sessions

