### 3.8 Statistical analysis

Clinical data analysis: Baseline data, demographic data and scale data will be analyzed by the SPSS 14.0 statistical software (SPSS Inc., Chicago, IL, USA). All analyses were based on the PP population. Chi-square test will be used to examine differences between groups (95% CI, 2-sided). The general linear model repeated measures procedure was used to test the differences in the repeated continuous variables (*Deqi* sensations) between the two groups.

Functional MRI image analysis: After data preprocessing conducted on SPM5 software, regional homogeneity and functional connectivity analysis will be performed to detect the modulation of different acupuncture interventions on pain-related functional networks at two time-points (prior to acupuncture, and after acupuncture treatment).

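### The Deqi comparison is tested by a complete-case procedure on the PP population, so patients lacking any one of the four readings contribute nothing to it

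*Protocol*

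**What the plan says.** Four statements in the protocol bear on this point.

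- **Course of treatment (3.4.3).** "After randomization the patients will receive 32 sessions of 30 minutes' duration over a period of 8 weeks". The weekly rate is a preference: "preferably 4 sessions in each week".
- **Deqi ratings (3.6.2).** These "will be collected after removing the needles during the 8^th^, 16^th^, 24^th^, and 32^nd^ sessions". The ratings follow session number, and the fourth falls at the final planned session.
- **Test (3.8).** "The general linear model repeated measures procedure was used to test the differences in the repeated continuous variables", with Deqi given as the variable meant. The same paragraph names SPSS 14.0 for the clinical data.
- **Analysis set (3.8).** "All analyses were based on the PP population".

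The protocol does not define the PP population. It also does not say whether the 32nd session means the 32nd one received or the 32nd slot in the plan. Section 3.2 gives 20 patients per group, and 3.3 lists three groups.

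**The concern.** GLM repeated measures treats the four readings as one multivariate response. A patient with one value missing is removed from the test altogether, including the values that were recorded. This is a property of the procedure; the protocol does not state it. Because the last rating sits at the last planned session, everyone who stops before session 32 lacks the fourth value.

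Section 3.4.2 asks for Deqi in every group, so the between-group test bears on how far needling sensation differed across the acupoint sets. If it rests on completers only, it loses precision in groups that are already small. It may also be biased if stopping is related to the sensation. The adverse events listed in 3.7, such as severe pain or fainting, are conceivable reasons to stop, but the protocol does not make that link.

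**Working it through.** **Inputs.** 32 sessions over 8 weeks, preferably 4 a week (3.4.3); ratings at sessions 8, 16, 24 and 32 (3.6.2); 20 patients per group (3.2). No attendance or dropout rate is given, so *p*, the chance that a session is missed and never made up, is an assumption.

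**The plan's own figure.** 8 weeks × 4 sessions = 32. At that rate the ratings fall at the ends of weeks 2, 4, 6 and 8, so the fourth reading is at the end of the course.

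**Share of patients with all four readings.** Assume that misses are independent and equally likely at each session, and that nobody stops treatment altogether.

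- Sessions counted as received: all 32 must take place, so the share is (1 − *p*)^32.
- Sessions as numbered planned slots: only slots 8, 16, 24 and 32 must be attended, so the share is (1 − *p*)^4.

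| *p* | Attendance | Counted as received | Of 20 | Numbered slots | Of 20 |
|---|---|---|---|---|---|
| 0.005 | 99.5% | 0.852 | 17.0 | 0.980 | 19.6 |
| 0.01 | 99% | 0.725 | 14.5 | 0.961 | 19.2 |
| 0.02 | 98% | 0.524 | 10.5 | 0.922 | 18.4 |
| 0.05 | 95% | 0.194 | 3.9 | 0.815 | 16.3 |

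Make-up sessions act by lowering *p*. If absences cluster in a few patients, more patients are complete at the same average rate, so the table leans towards the pessimistic side. Early stopping adds to the loss under both ways of counting.

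**Readings discarded.** Suppose *d* of 20 patients in a group lack only one reading.

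- Collected: 4(20 − *d*) + 3*d* = 80 − *d*.
- Used by GLM repeated measures: 4(20 − *d*) = 80 − 4*d*.
- Observed but discarded: 3*d*.

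For *d* = 2, the test uses 72 of 78 readings and discards 6. For *d* = 4, it uses 64 of 76 and discards 12. A likelihood-based model would use all 78 or all 76. A patient who stops between sessions 16 and 24 has two readings, and both are discarded.

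**Effect of the PP restriction.** If PP requires all 32 sessions, patients without a 32nd session are excluded before any model is fitted. GLM then loses nothing further, and a mixed model on the PP set recovers nobody. If PP admits shorter courses, GLM itself removes these patients. Either way the Deqi test rests on completers. Changing the model without changing the analysis set may therefore have no effect.

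**The case against.** The strongest case against is that the PP restriction, not GLM, may cause the loss, and that the PP definition and the handling of missing values commonly belong in an SAP, which is not shown. The first part stands, and it is why the analysis set has to change along with the model. The second part stands only in part. The protocol itself fixes the rating points, the procedure and the population, so the point concerns stated choices and not an absent detail. An SAP could still soften it, for example by imputation.

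A reader might infer more than the documents support:

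- **That one missed session removes a patient from the test.** This follows only if sessions are counted as received and the session is not made up. The protocol does not settle the numbering, and a weekly rate that is only preferred leaves room to move sessions within the 8 weeks.
- **That all four readings are lost.** A patient without a 32nd reading has at most three to lose. They leave one test but stay recorded and can be described.
- **That few patients would remain.** The figure of 3.9 of 20 is the worst case shown, under the harsher way of counting and an assumed 95% attendance without make-ups. It is not a forecast for this trial.
- **That completers are selected by tolerance of needling.** This is plausible but is not stated; sessions may be missed for unrelated reasons.
- **That ratings should move to calendar weeks.** Anchoring them to session number holds cumulative exposure constant and is a legitimate choice. A patient who stops early would have no week-8 value either.

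**Conclusion.** The point holds in limited form. The stated combination of a final rating at the last planned session, GLM repeated measures and a PP-only analysis confines the Deqi test to patients with all four readings. Each patient lacking one or more takes up to three observed readings out of it.

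The size cannot be fixed from the protocol. Over assumed attendance of 99% to 95% without make-ups, between 14.5 and 3.9 of 20 patients per group are complete if sessions are counted as received, and between 19.2 and 16.3 if they are numbered slots. These figures rest on independent misses at a common rate and leave out early stopping. The conclusion also assumes that missing Deqi values are not imputed. Any bias, as distinct from lost precision, requires a link between stopping and Deqi that the protocol does not establish.

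Deqi is a process measure and is not named as a primary outcome, so the priority is low to moderate.

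**What to change.** In 3.8, make two changes for Deqi together:

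1. Replace GLM repeated measures with a linear mixed model that has group, session (8, 16, 24, 32) and group by session as fixed effects, allows for correlation within patients, and uses every available reading.
2. State that this analysis includes all randomised patients with at least one Deqi reading, and is not confined to the PP set.

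Leave the collection points in 3.6.2 as they are.

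The cost is a change of wording and a different SPSS procedure, with no added visits or ratings. The model is valid if missing readings are missing at random given those observed. If patients stop because of sensations that were never rated, some bias would remain. Patients who stop before session 8 have no reading and still cannot contribute.

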### 3.7 Adverse events

Any adverse events, and how they are addressed, are recorded during the treatment periods. These adverse events include bleeding, hematoma, fainting, serious pain, and local infection. If patients suffer any serious adverse events, all details will be documented and reported to the IRB.

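### The adverse event window in Section 3.7 closes with the treatment phase at week 8, so late non-serious needle-site events have no planned capture and the two scans are not clearly covered

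*Protocol*

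**What the plan says.** Section 3.7 of the Protocol has three sentences that matter here. The first sets the recording window: "Any adverse events, and how they are addressed, are recorded during the treatment periods". The second lists the kinds of event expected: "These adverse events include bleeding, hematoma, fainting, serious pain, and local infection". The third deals with serious events and gives no time limit: "If patients suffer any serious adverse events, all details will be documented and reported to the IRB".

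The meaning of the window comes from the schedule. Section 3.4.3 states: "The total observation period within this study is 12 weeks for each patient". It describes a 4-week diary phase before randomization, then 32 sessions over 8 weeks, with 4 per week preferred. Its schedule table has only two phases, "baseline | treatment periods", and the second covers weeks 0 to 8. No phase follows it. Section 3.3 repeats the 12-week total and puts the last outcome measurement at week 8.

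On imaging, Section 3.3 says: "Resting-state fMRI scans will be performed on each group before and after treatment". Section 3.8 describes the same two time-points relative to acupuncture. Neither section fixes a day or week for either scan.

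**The concern.** The Protocol does not leave the recording window open for a later document to settle. It states one, and that window stops where the treatment phase stops. An analysis plan cannot repair this, because it cannot analyse events that were never collected.

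Two of the listed events, local infection and hematoma, may become apparent some time after the session that caused them. For most of the course this does little harm: at about four sessions a week the patient is soon seen again, and the window is still open. The final sessions are different, because the window closes within days of them.

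The scans raise a related question. They are study procedures in a 3 Tesla magnet, and Section 2.2.2 treats the magnetic field as a reason for screening. Yet scans described as before and after treatment do not sit comfortably in a window described as during it.

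What is at stake is how complete the non-serious safety record is.

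**Working it through.** **Inputs.** Observation period 12 weeks (Sections 3.3 and 3.4.3). Baseline 4 weeks, treatment 8 weeks, 32 sessions (Section 3.4.3). Three groups of 20 (Sections 3.2 and 3.3). Recording window equal to the treatment periods (Section 3.7).

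**Step 1. Reproduce the Protocol's total.** 4 + 8 = 12 weeks, which agrees with the stated period. 32 / 8 = 4 sessions per week, which agrees with the preferred frequency.

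**Step 2. Follow-up after the treatment phase.** 12 − 4 − 8 = 0 weeks.

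**Step 3. Time between the last session and the close of the window.** Week 8 covers days 50 to 56 after randomization. Assume four sessions in that week on separate days. The fourth then falls no earlier than day 49 + 4 = 53 and no later than day 56. The window stays open for 56 − 53 = 3 days at most and 56 − 56 = 0 days at least.

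**Step 4. Sessions with incomplete observation.** A session on day *d* has 56 − *d* days of recording left. The Protocol gives no onset times, so two values are assumed to show the range.

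| Assumed longest onset | Incompletely observed if | Sessions per patient | Share of 32 |
|---|---|---|---|
| 7 days | 56 − *d* < 7, i.e. day 50 or later | 4 | 4/32 = 12.5% |
| 3 days | 56 − *d* < 3, i.e. day 54 or later | 0 to 3, depending on session days | 0% to 3/32 = 9.4% |

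With 3 × 20 = 60 patients, the 7-day case covers 60 × 4 = 240 of 60 × 32 = 1,920 sessions. An early week-8 session still has up to 56 − 50 = 6 days of recording, so incomplete does not mean absent. No event rate is given, so these figures cannot be turned into a number of missed events.

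**Step 5. The scans.** No arithmetic applies. Read literally, a scan before treatment and a scan after treatment both lie outside a window that runs during treatment. Read against the schedule table, the first scan could fall between randomization and the first session, and the second within week 8. Both would then lie inside the weeks 0 to 8 block. The text does not decide between these readings.

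**The case against.** The strongest reply is that the gap is small and that several broader readings go further than the text. Most of this stands.

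- **End of the window.** A reader might infer that observation ends with session 32. It does not: the treatment phase is a calendar block ending at week 8, which may be up to 3 days later under the assumption in Step 3.
- **Later contacts.** There may be a contact after the last session, since outcomes are measured at week 8 and a scan follows treatment. If that scan falls by week 8, it is a contact inside the block. If it falls later, patient contact goes beyond the 12 weeks and the zero-week figure describes planned observation, not all contact. Either way, Section 3.7 does not say that adverse events are asked about at that visit, and an event first appearing after week 8 is outside the stated window.
- **Scans.** A reader might infer that both scans are excluded from safety recording. Without scan dates this holds only on the literal reading, so the defect is unclear coverage and not a stated exclusion.
- **Serious events.** A reader might infer that a serious late infection or a serious scan event would go unreported. The serious-event sentence has no time limit, so the documents do not support that. The gap concerns non-serious events.
- **Early stopping.** A reader might infer that recording ends when a patient stops treatment. Section 3.4.3 uses the term for a study phase, not a personal interval, so this is an inference. The Protocol does not settle the point either way.
- **Importance.** The stated purpose is to compare brain responses and relate them to clinical efficacy, and nothing in that comparison depends on the window. This is correct and limits the weight of the point.

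**Conclusion.** The point holds in a limited form. Section 3.7 states a recording window that is too narrow: it covers weeks 0 to 8, with 0 weeks of planned follow-up afterwards. Non-serious delayed needle-site events from the final sessions that first appear after week 8 have no planned capture. Coverage of the two scans is unclear.

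The zero-week result follows directly from the Protocol's own schedule. The session shares (12.5% at 7 days, 0% to 9.4% at 3 days) rest on assumed onset times and on four week-8 sessions held on separate days. The consequence is confined to the safety record. It is worth correcting because the change is cheap, not because any conclusion on efficacy or imaging is at risk.

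**What to change.** In Section 3.7, replace the current window with one that starts at the first study procedure, the pre-treatment scan, and ends at the later of the post-treatment scan visit and a short fixed interval after the patient's last session. The sponsor should choose and state that interval. Say that the window applies to every patient who received at least one session, including those who stop early.

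Bring the 12-week observation period in Sections 3.3 and 3.4.3, and the schedule table, into line with the new end point.

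The cost is an adverse event entry on the form at each scan visit, possibly one telephone contact per patient, and a slightly longer observation period. Because the 12-week total appears in two sections, this takes more than a single-sentence edit. The sample size and efficacy analyses stay as they are.

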### 3.8 Statistical analysis

Clinical data analysis: Baseline data, demographic data and scale data will be analyzed by the SPSS 14.0 statistical software (SPSS Inc., Chicago, IL, USA). All analyses were based on the PP population. Chi-square test will be used to examine differences between groups (95% CI, 2-sided). The general linear model repeated measures procedure was used to test the differences in the repeated continuous variables (*Deqi* sensations) between the two groups.

Functional MRI image analysis: After data preprocessing conducted on SPM5 software, regional homogeneity and functional connectivity analysis will be performed to detect the modulation of different acupuncture interventions on pain-related functional networks at two time-points (prior to acupuncture, and after acupuncture treatment).

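### The clinical analyses are stated as per-protocol only, with PP undefined and no analysis of all randomised patients, so the three-arm comparison is open to post-randomisation selection bias

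*Protocol*

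**What the plan says.** Section 3.3 describes three groups and allocation by chance: "Randomization: using a computer-generated randomization sequence". Section 3.2 gives the size as "20 subjects in each group", without an effect size, power or dropout allowance. Treatment follows allocation (section 3.4.3): "After randomization the patients will receive 32 sessions of 30 minutes' duration over a period of 8 weeks".

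Section 3.8 has two paragraphs. The first opens "Clinical data analysis: Baseline data, demographic data and scale data will be analyzed by the SPSS 14.0 statistical software" and continues with the population rule: "All analyses were based on the PP population". It then names a chi-square test for group differences and a repeated-measures general linear model for needling sensations. The second paragraph covers imaging and begins "Functional MRI image analysis: After data preprocessing conducted on SPM5 software, regional homogeneity and functional connectivity analysis will be performed"; it names no population.

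The protocol does not say what makes a patient per-protocol. It gives no minimum number of sessions, no diary-completeness rule and no list of deviations. No intention-to-treat or full analysis set appears, even as a sensitivity analysis.

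**The concern.** Randomisation makes the three groups comparable at the moment of allocation. A per-protocol set selects patients by what happens afterwards. In a course of 32 sessions over 8 weeks, staying within protocol can plausibly depend on whether the headaches improve and on how well the needling is tolerated. Both may differ between the sets of acupoints being compared. If so, the patients left in each group are no longer comparable, and a difference between groups can arise with no difference in effect.

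Two features make this more serious. Because PP is undefined in the protocol, who is excluded could be settled after outcomes are known. And because no all-randomised analysis is stated, a reader of the results would have nothing to set beside the PP result. The patient blinding and blinded data analysis in section 3.3 do not remove this bias, since it comes from who remains in the data and not from how outcomes are rated.

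The trial's purpose includes relating clinical efficacy to brain response, so a distorted clinical comparison would carry into that aim as well.

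**Working it through.** **The plan's own figure.** The 20 per group cannot be reproduced, because no effect size, SD, power or dropout is given. The point does not rest on it; 20 is used below only as the arm size.

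**Assumptions, none of them from the documents.** Two arms of 20; outcome normal with SD 1, higher is better; no true difference; k = 2, 3 or 4 patients excluded from one arm and none from the other; two-sided 5% two-sample t-test. The t-test is a simple stand-in for a pairwise comparison and is not a test the protocol names.

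**Shift in the mean.** The 20 values sum to zero in expectation. If the removed values have expected sum −S, the remaining mean is S / (20 − k).

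*Case 1: removed at random from the lower half of the arm.* The ten lowest of 20 standard normal values average −0.767, so S = 0.767k.
- k = 2: 1.534 / 18 = 0.085
- k = 3: 2.301 / 17 = 0.135
- k = 4: 3.068 / 16 = 0.192

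*Case 2: the very worst k.* The four lowest expected values are −1.8675, −1.4076, −1.1309 and −0.9210.
- k = 2: 3.2751 / 18 = 0.182
- k = 3: 4.4060 / 17 = 0.259
- k = 4: 5.3270 / 16 = 0.333

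**Type I error, by simulation (200,000 runs per row).**

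| Excluded from one arm | Case 1: shift, type I error | Case 2: shift, type I error |
|---|---|---|
| 2 of 20 | 0.085 SD, 5.4% | 0.18 SD, 10% |
| 3 of 20 | 0.135 SD, 6.4% | 0.26 SD, about 14.5% |
| 4 of 20 | 0.19 SD, 8.0% | 0.33 SD, 20% |

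**Losses in both arms.** Here patients below the median are excluded at random, at overall rates given for the two arms (100,000 runs):
- 0% v 10%: 0.09 SD, 5.8%
- 10% v 20%: 0.11 SD, 6.3%
- 0% v 20%: 0.20 SD, 9.2%
- 10% v 10%: no shift, 5.0%

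**Direction.** If the best k leave one arm instead of the worst, the shift has the same size with the opposite sign (−0.18 to −0.33 SD).

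**On a response rate**, which suits the chi-square test the protocol does name: let the true rate be 50% in both arms (assumed) and exclude a fraction e of non-responders. The PP rate is 0.5 / (0.5 + 0.5(1 − e)).
- e = 0 v 0.2: 50.0% v 0.5 / 0.9 = 55.6%
- e = 0.1 v 0.4: 0.5 / 0.95 = 52.6% v 0.5 / 0.8 = 62.5%

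Both differences are spurious.

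**The case against.** The best defence is that this is a small mechanistic imaging study with no declared primary clinical endpoint, that a PP definition is commonly left to a SAP, and that section 3.6.2 already asks all patients for diaries at 4 and 8 weeks, with no exemption for those who stop. With few or balanced exclusions the bias may be negligible.

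Part of this stands. A SAP could supply the definition, the size is unknown, and the diary schedule makes the remedy easier. But the choice of population is stated outright in the protocol. A SAP that made an all-randomised analysis the main one would contradict that sentence, so the sentence has to change.

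Four stronger readings are tempting and are not supported:

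- **That safety is also restricted to PP patients.** Only the word 'all' suggests it. The sentence sits under clinical data, introduced as baseline, demographic and scale data. Section 3.7 says "Any adverse events, and how they are addressed, are recorded during the treatment periods", with no PP limit and no statistical safety analysis. A claim that adverse-event rates will be biased downward has no basis in the text.
- **That the imaging comparison is PP.** The imaging paragraph names no population, so this is open.
- **That patients who stop the course are certainly removed.** That is the usual meaning of PP, but the protocol sets no completion threshold.
- **That the analysed sample must fall below 20 per group.** Section 3.2 does not say whether 20 is the number randomised or analysed.

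**Conclusion.** The point holds for the clinical data. PP is the only population stated, it is undefined in the protocol, and no analysis of all randomised patients is planned there, so the comparison of the three groups is exposed to selection after randomisation.

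How much this matters depends on how many patients are excluded, how unevenly, and how strongly exclusion follows outcome; the documents settle none of these. For 2 to 4 one-sided losses of poor responders, the plausible span runs from a small distortion to a near worst case, in which a nominal 5% test rejects up to one time in five. The upper end should not be quoted alone. Neither the presence nor the direction of bias can be predicted from the documents; what is certain is that the stated rule gives no protection against it.

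**What to change.** Replace the population sentence in section 3.8 with:

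> The main clinical comparisons include all randomised patients in their allocated group, using all available diary and scale data; the diaries and scales at weeks 4 and 8 are collected from all patients, including those who stop needling. fMRI comparisons include every patient with usable scans, by allocated group. A per-protocol analysis, with its definition fixed before unblinding, is a sensitivity analysis.

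The imaging sentence fills a silence in the protocol; it does not correct a stated rule. The follow-up has to be arranged in advance, because diary entries that were never made cannot be recovered later.

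The cost is a change of wording, some effort to follow patients who stop treatment (at time points already scheduled), and possibly a slightly diluted effect estimate. No extra patients or scans are needed.

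### Chi-square is the only between-group test in section 3.8 that covers the headache-diary and scale outcomes, and it does not suit counts and scores

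*Protocol*

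**What the plan says.** Under the clinical data heading of Protocol section 3.8, the plan first states which data are covered: "Baseline data, demographic data and scale data will be analyzed by the SPSS 14.0 statistical software". After a sentence on the per-protocol population comes the test: "Chi-square test will be used to examine differences between groups (95% CI, 2-sided"). No variable, category or responder definition goes with it. The next sentence reads "The general linear model repeated measures procedure was used to test the differences in the repeated continuous variables". It then names Deqi sensations in parentheses as the variables concerned, and refers to two groups.

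Section 3.3 defines three groups, the third being "Group C:acupuncture at acupoints on other meridians", and section 3.2 plans "20 subjects in each group".

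The clinical data are of mixed type:
- **Diary (3.6.2):** attack start and stop times, then "the intensity (VAS), the frequency, the location and the cause of headache, associated symptoms in each migraine attack". Medication use is also recorded: "The patients document whether or not they take the medicine during treatment periods".
- **Scales (3.6.2):** HIT-6, SAS and SDS at baseline, week 4 and week 8.
- **Baseline (3.6.1):** gender alongside age, vital signs and blood results.

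**The concern.** The protocol is not silent on how groups are compared clinically. It lists the scale data, names one test of group differences without restriction, and gives its only continuous-data model to a process measure (Deqi). The diary and the three scales are also repeated and quantitative, yet the only test left for them is one for contingency tables.

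Followed as written, the clinical comparison goes one of two ways. Raw values can be cross-tabulated by group, which gives a sparse table. Or they can be cut into categories, which loses information and leaves the cut-point open to choice after the data are seen. In neither case does the test itself give a mean difference with the 95% CI that the same sentence mentions.

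**Working it through.** **No figure of the plan's own to reproduce.** Section 3.2 gives 20 per group without an endpoint, effect size, SD or power. All effect sizes below are assumptions for illustration. The inputs from the protocol are 20 per group and three groups (3.2, 3.3) and a two-sided test with 95% CI (3.8), read as a 5% level.

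**1. Which test covers which variable**

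| Variable | Type | Test that 3.8 offers |
|---|---|---|
| Gender, headache location, cause, associated symptoms, medication yes/no, adverse events | categorical | chi-square, suitable in type |
| Attack frequency, duration, VAS, HIT-6, SAS, SDS, age, vital signs, blood results | count, time or score | chi-square only |
| Deqi sensations | repeated continuous | GLM repeated measures, for two groups |

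**2. Chi-square on raw values.** With three equal groups, the expected count in a cell is one third of the number of patients who share that value. It reaches 5 only if 15 of the 60 patients have the same value. Even for attack frequency limited to 2 to 8 (seven values, inclusion criterion 2), the average expected count is 60 / 7 / 3 = 2.9.

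Simulated integer scores (normal, assumed SD 6 points, one of three groups shifted by 0.8 SD) gave about 3 to 4% power for chi-square and 72 to 74% for ANOVA. With no true difference, chi-square rejected about 1% of the time, not 5%. No expected count reached 5.

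**3. Chi-square on categorised values: information kept.** For a normal outcome cut at quantile q, relative efficiency is φ(z_q)² / [q(1 − q)].
- Median: 0.399² / 0.25 = 0.64, a loss of 36%. Twenty patients are then worth about 20 × 0.64 = 13.
- 25th percentile: 0.54, a loss of 46%.
- 20th percentile: 0.49, a loss of 51%.
- 10th percentile: 0.34, a loss of 66%.

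**4. Power, two groups of 20, pooled-median split (simulation)**

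| Assumed difference | t-test at 5% | t-test at the chi-square's true size | chi-square |
|---|---|---|---|
| 0.7 SD | 58% | 46% | 31% |
| 0.9 SD | 79% | 70% | 51% |

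The middle column is needed because the chi-square test is discrete here. A 13/7 split against 7/13 gives χ² = 40 × (13² − 7²)² / 20⁴ = 3.6, below 3.84. A 14/6 split gives 40 × (14² − 6²)² / 20⁴ = 6.4. Rejection therefore starts at 14/6, and the true size is about 2.5%. The gap is 27 or 28 points as the tests would be run, and 15 or 19 points at matched size.

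**5. Three groups, one shifted (simulation).** ANOVA against a 3 × 2 chi-square at the pooled median gives 72% against 51% at 0.8 SD, and 90% against 71% at 1.0 SD. Both tests hold their size here (5.1% and 4.9% with no difference), so discreteness does not explain these gaps of 21 and 19 points.

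**6. In patients.** For 80% power at an assumed 0.8 SD, comparing two means needs 2 × (1.96 + 0.84)² / 0.8² = 24.5, so 25 per group. Cutting midway between the means turns 0.8 SD into proportions of 34.5% and 65.5%, and the usual formula for two proportions then needs 40 per group. That is 60% more.

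**The case against.** The strongest reply is that section 3.8 never says that scores go to chi-square. It assigns the scale data to a software package, and the chi-square sentence names no variable. The following sentence separates out repeated continuous variables, so the authors do distinguish data types. Chi-square may be meant only for categorical items, with the test for scores left to an analysis plan not seen here. The first part stands: nothing expressly prescribes chi-square on raw scores. But the sentence is unrestricted, comes just after the scale data are listed, and is the only one that can apply to them. An analyst following the text has no other test to use.

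Some stronger readings are tempting but are not supported:
- **That chi-square is the only between-group test for any clinical data.** The GLM for Deqi sensations is a second one.
- **That practically all clinical outcomes are numeric.** Several are categorical, and chi-square suits them.
- **That most of the information is lost.** A median split loses about 36%. The loss passes half only for cuts near or beyond the 20th or 80th percentile. Cross-tabulating raw scores does lose nearly all power, but the text does not say that this is intended.
- **That efficacy could then not be related to brain response.** Patient-level changes from the diary and scales are collected whatever group test is used.

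**Conclusion.** The point holds for the headache-diary outcomes, the scale outcomes and the numeric baseline data: the only between-group test that section 3.8 offers for them does not fit their type, and no categorisation is defined. Under assumed normal data with 20 per group, a median split costs about 15 to 20 points of power at matched size for differences of 0.7 to 0.9 SD, and nearly 30 points as the tests would actually be run. These figures depend on the assumed effect, the distribution and the cut-point, none of which the protocol states.

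This should be fixed, but it does not undermine the trial. The stated purpose centres on brain activity, and the regional homogeneity and functional connectivity analyses in 3.8 are specified separately and are unaffected.

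**What to change.** In section 3.8:
- Restrict chi-square to categorical items, with Fisher's exact test where expected counts are below 5.
- For attack frequency, duration, VAS, HIT-6, SAS and SDS, name a model with the three-level group factor, adjusted for the baseline value already collected. This can be ANCOVA or a repeated measures model over weeks 4 and 8, with a count model for attack frequency if needed.
- Report the A-B and A-C differences with 95% CIs.
- Change the reference to two groups in the GLM sentence to three, in line with section 3.3.

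The cost is a few lines of text. Design, visits and data collection do not change.
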